## 1. Rethink Pulmonary Rehabilitation – the REPORT Study

### 2. Rationale

The common disease chronic obstructive pulmonary disease (COPD) is closely associated with smoking, and costs DKK 8.5 billion annually in citizens' contact and treatment within the health care system^1. It is estimated that 12% of all adult Danes above the age of 45 years have COPD. Improved treatment options and increasing life expectancy imply that the number of people with rehabilitation-requiring COPD increases and places increased demands on best possible use of the limited resources in the health care system, not least in the years to come.

Pulmonary rehabilitation (PR) is one of the cornerstones of care for people with COPD together with smoking cessation and medical treatment. There is robust evidence that pulmonary rehabilitation improves exercise capacity, enhances health-related quality of life (QoL) and reduces healthcare utilization. PR is strongly recommended in guidelines for COPD management. More than 85% of European countries have implemented an outpatient model, including Denmark, where participants attend two to three sessions each week of supervised exercise and self-management training for a period of eight weeks or more. Despite the compelling evidence for its benefits, pulmonary rehabilitation is delivered to less than 30% of patients with COPD who would benefit from the intervention. Referral to PR and access to PR are particularly challenging, and especially for those with the most progressed stages of the disease.

We recently completed a randomized clinical trial showing that approximately 1,100 patients annually are offered conventional hospital- and community-based PR during routine consultations in the Capital Region of Denmark, but of these at least 700 patients decline participation. Frequent transport to the center-based program, in the setting of distressing dyspnea and mobility limitation, is regularly reported as an access-barrier to attendance in hospitals and community health-care centers and yet the delivery of PR has not changed significantly in 30 years.

Much is unknown regarding COPD patients unable to participate in conventional PR programs as no studies have been conducted to specifically intervene in this group. Important knowledge in terms of symptoms (respiratory, anxiety, depression, impaired QoL, body pain and sleep quality) and physical functioning (exercise capacity and objectively measured physical activity), and response to alternative rehabilitation models is a black box with no substantial research, except for studies on qualitative perceived enablers and barriers. There is a key gap in evidence for new rehabilitation models. The effectiveness and feasibility of home-based pulmonary rehabilitation (HPR) and pulmonary tele-rehabilitation (PTR) have never been investigated in this specific group "conventional none-participant" of patients with COPD, but it is strongly endorsed as an essential research scope by the American Thoracic Society/European Respiratory Society.

Home-based pulmonary rehabilitation and PTR^14 are two alternative models using health-care supportive technology that have proven equivalent or non-inferiority to the conventional PR programs in patients with COPD who are able and willing to participate in conventional PR.

However, for HPR and PTR to fulfil their promises, they must be accessible to the target groups, be well accepted by users, deliver the essential components of PR, and be easy to implement. Furthermore, the results after the interventions must be of clinical relevance, i.e. beneficial and superior to the current 'usual care' (medication and scheduled follow-up control). Specific tools and delivery models that actively include and help patients with COPD to improve and subsequently maintain their symptom control and functional level are needed. Only out-patient centered PR exists, and alternative rehabilitation and maintenance programs that overcome accessibility barriers do not exist. The lack of public initiatives addressing this limited access to rehabilitation can contribute to inequality in health in already exposed patients with progressed COPD. Thus, there are good reasons to improve access and awareness of potential benefits from new delivery models of pulmonary rehabilitation and maintenance programs.

We use two evidence-based structured model of HPR and PTR with health-care supportive technology to meet these requirements and to test the clinical efficacy and model acceptance. The aims of this study are to (1) compare the clinical benefits of the two rehabilitation models with 'usual care'; (2) investigate adherence to and effect from an exercise maintenance-program; (3) to qualitatively investigate the patients' experience with the intervention and maintenance program; (4) to investigate the program costs and explore the way in which the exercise programs are carried out and adapted. These aims are elaborated in the following section.

## **2.1 Objectives and hypotheses**

**2.1.1 Primary objective (RCT- study I)** of the REPORT study is to evaluate the effects of structured home-based pulmonary rehabilitation (HPR) and supervised pulmonary tele-rehabilitation (PTR) on respiratory symptoms, quality of life, functioning and physical activity in patients with moderate to severe COPD who are unable or unwilling to access the conventional hospital- and community-based PR programs.

**2.1.2 Our hypotheses** are that HPR and PTR will lead to respiratory symptom relief in the patients and that PTR and HPR will be equivalent to each other and superior to usual care, that is the a control group (CON - no intervention) among patients unable to access conventional rehabilitation programs.

### **2.1.3 Aims for the overall research project**

1. To investigate equivalent effect of HPR and PTR and superiority to CON on patient-reported health parameters such as quality of life, anxiety-depression symptoms, sleep quality, fatigue, muscular-skeletal pain, physical activity and functioning level (**RCT- study I**) (**table 2**).
2. Monitor and retrieve number of hospital admissions, length of stay and mortality from baseline throughout the follow-up period through the National Health Data Authorities (**RCT- study I**).
3. To investigate adherence to and effect from an exercise maintenance-program (similar healthcare-technologies) on self-reported health parameters of quality of life, anxiety-depression symptoms, sleep quality, fatigue, muscular-skeletal pain, physical activity and functioning level (**Maintenance - study II**).

4. Qualitatively investigate the participant experience with the intervention and maintenance program and its impact on their everyday life involving social, structural, cultural and gender factors with the following aims.

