***Please read appendix 1. for information on the test procedure from the physical functioning test (Danish)***

## **3.6 Sample size and statistics**

*(performed by biostatistician [name], Clinical Research Centre, University Hospital Hvidovre)*

Three primary pairwise comparisons are made in the study, equivalence test between the two interventions and the superiority test for each intervention compared to the control group for the primary outcome of respiratory symptoms (COPD assessment test). Sample size estimation for the equivalence is based on a t-test with equivalence margin of -2.5 to 2.5 (clinically relevant difference), standard deviation (SD) of 4.5, power of 80% and significance level of 5%, and estimated 56 patients necessary in each group. For both, superiority tests a minimal clinical difference of 2.5, SD of 4.5, power of 80% and significance level of 5% were used in a two-sample t-test, with fixed sample of 56 patients in the intervention groups. This yields a necessary size of 36 patients in the control group. The sample size is increased by 25% in each group to account for expected withdrawal and loss of power from adjustment and thus a total of 185 (70/70/45) patients. Power estimations for all secondary outcomes are based on the decided inclusion of 185 patients, expected standard deviation and established minimal clinical important difference (MCID) (**Table 2**).

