**3.6.1 Statistical analyses plan**

Analyses of the outcomes will be performed by the trial statistician ([name]) who is blinded to the treatment allocations. Secondary analyses will be performed by Postdoctoral fellow, PhD [name].

Baseline data will be reported as averages and standard deviations (medians and interquartile ranges) or frequencies and proportions as appropriate. Data analyses of both primary and secondary endpoints will be performed using intention-to-treat analyses. Additionally, per-protocol analyses including patients who complete  $\geq 70\%$  of the PTR and HPR rehabilitation program will be performed. Reporting will follow the CONSORT (Consolidated Standards of Reporting Trials) Statement for non-pharmacologic trials. Differences between the groups' changes of primary and secondary outcomes (10-weeks from baseline; 35-weeks from baseline and 75-weeks from baseline) will be analyzed by mixed effect models. The models include adjustment for treatment groups, age, sex, BMI, FEV1, Charlson Comorbidity Index and smoking status, and a random effect recruitment site. To account for possible regression to the mean effect, the baseline measure for the outcome will be included as a fixed effect variable in the models. Normal distribution of the model residuals is evaluated by inspection of Q-Q plots. All data are considered missing at random and because of this, the ignorability assumption for the likelihood estimator is used to account for missing data. The number of used datasets will be transparent. Survival are visualized by Kaplan-Meier curves. Group differences on number of patients being adherent, hospitalization and death are analyzed using chi-squared test. No interim analysis will be made. Statistical analyses are carried out using R 3.2.2 (R Foundation for Statistical Computing, Vienna, Austria). P-values of less than 0.05 are considered statistically significant.

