| Qualitative data                      |                                              |                                                                          |                                   |                        |                        |
| Qualitative study                            | Interview
Survey
Observation           | Continuously during the recruitment, intervention and maintenance period |                                   |                        |                        |

| Table 2. Anticipated power on secondary outcomes – superiority to control |                                                                  |                                                                                                                                                                                                                                                                             |                                                                                                                                                                                             |                                                       |
|---------------------------------------------------------------------------|------------------------------------------------------------------|-----------------------------------------------------------------------------------------------------------------------------------------------------------------------------------------------------------------------------------------------------------------------------|---------------------------------------------------------------------------------------------------------------------------------------------------------------------------------------------|-------------------------------------------------------|
| Variables                                                                 | Instrument                                                       | Subscales                                                                                                                                                                                                                                                                   | Cronbach's alpha                                                                                                                                                                            | Hypothesized Difference/ SD (anticipated power)       |

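### Aim 1 sets HPR–PTR equivalence on the secondary outcomes, but the protocol states an equivalence test and margin for CAT only, so its stated secondary analysis cannot answer that aim

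*Protocol*

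**What the plan says.** Section 2.1.3, Aim 1, assigned to RCT study I: "To investigate equivalent effect of HPR and PTR and superiority to CON on patient-reported health parameters such as quality of life, anxiety-depression symptoms". The sentence goes on to sleep quality, fatigue, pain, physical activity and functioning level, and points to Table 2. Section 7 likewise places HPR–PTR equivalence inside an objective that covers quality of life, functioning and physical activity.

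Section 3.6 ties the formal comparisons to CAT: "equivalence test between the two interventions and the superiority test for each intervention compared to the control group for the primary outcome of respiratory symptoms". The margin is also for CAT: "equivalence margin of -2.5 to 2.5 (clinically relevant difference), standard deviation (SD) of 4.5, power of 80% and significance level of 5" per cent, leading to "estimated 56 patients necessary in each group".

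Table 2, which Aim 1 cites, is headed "Anticipated power on secondary outcomes – superiority to control". It gives a hypothesised difference, an SD and an anticipated power for most instruments. It has no HPR–PTR margin and no equivalence power. MFI-20 and PSQI are labelled exploratory, and the Guralnik test has no established difference.

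Section 3.6.1 has mixed models analyse "Differences between the groups' changes of primary and secondary outcomes", and its only stated criterion is "P-values of less than 0.05 are considered statistically significant".

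**The concern.** The aim, the table it cites and the stated decision rule do not fit together. A test of a between-group difference has equality as its null hypothesis. It can show that HPR and PTR differ, but failing to reject does not show that they differ by less than a relevant amount. An equivalence conclusion needs a margin and a test or confidence interval set against it, as section 3.6 has for CAT. Aim 1 asks the equivalence question of about seven further domains, and the protocol supplies neither element for them. For fatigue, sleep and the Guralnik test it does not even state a relevant difference.

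What is at stake is how a non-significant HPR–PTR result on quality of life, pain or daily steps would be reported. If it were taken as equivalence, a real and relevant disadvantage of one delivery model could pass unnoticed more often than the 5% that a margin rule allows.

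**Working it through.** **Inputs.** CAT margin 2.5, SD 4.5, 80% power, 5% level and 56 per arm come from section 3.6. The same section gives the inflation: "The sample size is increased by 25% in each group to account for expected withdrawal and loss of power from adjustment", so 56 × 1.25 = 70 per intervention arm. Differences and SDs for the other outcomes come from Table 2; the TUG and gait-speed figures are matched to their tests by their order in the cell. Two-sided testing is assumed, because section 3.6.1 does not state sidedness.

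**1. Reproduce the protocol's figure.** For two one-sided tests at 5% each with true difference zero:

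n = 2[SD(z₀.₉₅ + z₀.₉₀)/margin]² = 2[4.5(1.645 + 1.282)/2.5]² = 2 × 5.268² = 55.5, hence 56.

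The t-based power at 56/56 is 0.798. Section 3.6 therefore describes a genuine margin test, for CAT.

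**2. How often would a difference test miss the Table 2 difference between HPR and PTR?** With d = difference/SD and n per arm, the noncentrality is λ = d/√(2/n). The result is non-significant when |T| ≤ t₀.₉₇₅ on 2n − 2 degrees of freedom.

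Example, EQ5D-VAS: d = 8/16 = 0.50.
- n = 56: λ = 0.50/0.189 = 2.646, critical t = 1.982, probability of non-significance 25.4%.
- n = 70: λ = 0.50/0.169 = 2.958, critical t = 1.977, probability 16.4%.

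| Outcome | Difference/SD | d | Non-significant, 56/56 | Non-significant, 70/70 |
|---|---|---|---|---|
| Steps per day | 1100/2262 | 0.486 | 27.7% | 18.5% |
| EQ5D-VAS | 8/16 | 0.500 | 25.4% | 16.4% |
| BPI-intensity | 2/4 | 0.500 | 25.4% | 16.4% |
| TUG | 1.4/2.4 | 0.583 | 13.6% | 7.1% |
| 6MWT | 26/44.5 | 0.584 | 13.5% | 7.0% |
| HADS-A, HADS-D | 1.5/2.5 | 0.600 | 11.8% | 5.9% |
| Hand grip | 5.0/7.3 | 0.685 | 5.1% | 2.0% |
| Sit-to-stand | 2.0/2.5 | 0.800 | 1.3% | 0.3% |
| Gait speed | 0.11/0.13 | 0.846 | 0.7% | 0.1% |

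MFI-20, PSQI and the Guralnik test have no stated difference, so nothing can be computed for them.

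**3. What would a margin rule achieve?** Take the Table 2 difference as the margin (an assumption), a true difference of zero, and each one-sided test at 5%. Power is then approximately 2Φ(λ − t₀.₉₅) − 1. For EQ5D-VAS at 56/56 this is 2Φ(2.646 − 1.659) − 1 = 0.676; the t-based calculation gives 0.675.

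| Outcome | Equivalence power, 56/56 | 70/70 |
|---|---|---|
| Steps per day | 64% | 78% |
| EQ5D-VAS | 68% | 81% |
| 6MWT, TUG | 85% | 93% |
| HADS-A, HADS-D | 87% | 94% |
| Hand grip | 95% | 98% |

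**The case against.** The strongest reply is that the protocol never says a non-significant difference will be called equivalence. Section 3.6 shows that its authors know equivalence needs a margin. The mixed-model sentence in 3.6.1 covers the primary outcome as well, so it evidently sits beside a margin test rather than replacing it. A p-value below 0.05 could come from an equivalence test, and a separate SAP could set secondary margins. Table 2 already holds candidate values, and section 3.6 describes them as established minimal important differences.

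Much of this stands. A reader might infer that p>0.05 will be taken as equivalence; no text says so, and the point here is only that the stated rule cannot support the conclusion. A reader might also take the miss rate to be one in four across the secondary outcomes. That figure holds for three outcomes with 56 evaluable per arm. Section 3.6 bases secondary power on all 185 patients, which gives 16–19% for those three. Nor do the documents support extending the problem to weeks 35 and 75: Aim 1's equivalence belongs to study I, whose primary endpoint is at week 10, and the maintenance aim makes no equivalence claim.

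What does not stand is that this is merely detail left to an SAP. Aim 1 cites a table that covers only the superiority half of that aim. Adding margins elsewhere would leave that mismatch in place. Labelling fatigue and sleep exploratory in Table 2 does not take them out of the aim.

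**Conclusion.** The mismatch holds. Aim 1 sets HPR–PTR equivalence on secondary outcomes, and neither the table it cites nor the stated criterion can answer it. Were non-significance read as equivalence, a true difference of the Table 2 size would be missed in 16–28% of trials for EQ5D-VAS, BPI-intensity and steps, and in 6–14% for HADS, 6MWT and TUG. For hand grip, sit-to-stand and gait speed the rate is about 5% or less, so little is at risk there. A margin rule caps false equivalence at 5% when the true difference equals the margin.

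These rates assume 56 to 70 evaluable per arm, an unadjusted two-sided 5% t-test, the Table 2 SDs, and a true difference exactly at the Table 2 value. The baseline adjustment planned in 3.6.1 would lower them to the extent that baseline predicts outcome. The primary CAT comparison is unaffected.

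**What to change.** Choose one of two routes before HPR–PTR results are seen.

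1. Restrict the equivalence aim to CAT, and report the secondary HPR–PTR differences as estimates with confidence intervals.
2. Keep secondary equivalence, and state in 3.6.1 that:
   - it is concluded at week 10 only if the 90% CI of the adjusted HPR–PTR difference lies wholly within a pre-stated margin, namely the Table 2 difference where one exists;
   - p>0.05 is not evidence of equivalence;
   - MFI-20, PSQI and the Guralnik test carry no equivalence claim.

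Under the second route, the BPI-intensity entry must first be reconciled: a difference of 2 with SD 4 sits beside a scale given as 0–100 mm. Its stated power of 0.71 also differs from the 0.81 given for EQ5D-VAS at the same ratio. An equivalence-power column in Table 2 would show which claims are weakly supported.

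The cost is wording and, for the second route, one table column; visits, data and models stay the same. The downside of the second route is that some claims become harder to reach: with no true difference, power for EQ5D-VAS and steps is about 64–68% at 56/56 and 78–81% at 70/70. The first route gives up secondary equivalence claims altogether.

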### **3. Methodology – Study I and II**

#### **3.1 Design**

The REPORT study is designed as a multi-center three-arm randomized controlled trial, with a subsequent maintenance program.

#### **3.2 Study population**

A total of 185 patients with moderate to very severe COPD who are unable to access the conventional hospital- and community-based PR programs when offered during routine consultations will be included from seven hospitals in the Capital Region, through general practitioners, healthcare centers and advertising through the Danish Lung Association to get a broad representative sample fulfilling our defined inclusion and exclusion criteria. During inclusion, baseline self-reported symptoms, functional capacity and physical activity is measured. Hereafter each participant is randomly assigned to one of the three arms in the study; HPR, PTR or CON. The HPR and PTR interventions begin within seven-to-ten days after randomization and patients participate in the 10-week assigned intervention and thereafter continue in a self-maintenance program for another 65-weeks (approx. 15-months). Self-reported respiratory symptoms constitute the primary outcome, assessed at the 10-week follow-up visit (primary endpoint). Follow-up assessment are done 10, 35 and 75 weeks (primary endpoint for the maintenance study) from baseline.

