### **3.6.2 Randomization**

The randomization allocation to HPR, PTR, CON is performed using block randomization with a randomized block size of 6 and 12 in random order. The randomization list will be generated in REDCap by the trial statistician and is not accessible to investigators involved in the conduct of the study until the database has been unlocked.

After written informed consent and completion of study assessments, patients are randomized to either HPR, PTR or CON. The target number of patients randomized to each group is 70, 70 and 45 respectively. After identification of an eligible patient, the patient is assigned a randomization number as identifier throughout the study. The participants are informed about which group they are randomized to by email and phone call. The patients in the three groups begin their assigned intervention within seven to ten days after randomization.

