## **3.7 Interventions (also read figures in appendices 1)**

### **3.7.1 Pulmonary Tele-Rehabilitation (PTR)**

The PTR intervention is supervised by skilled physiotherapists and respiratory nurses with at least 2-years of substantial experience with PR and delivered via a virtual platform at Bispebjerg and Hvidovre Hospital to a group of 4–6 patients who exercise at home and communicate via tablet with Center for IT and Medico (CIMT) approved communication software. Each session is 60 min; 35 min of exercise and 25 min of patient education, two times per week for the duration of 10 weeks. The specific exercises used are evidence-based as they have been used in several intervention studies on patients with severe or very severe COPD and involves larger muscle groups with 50/50% exercises for upper and lower extremities, respectively. Volume, intensity and content specified for the exercise protocol is in accordance with both national and international exercise recommendations. The exercise sessions include relative progression every fourth week, as the patients are expected to improve their mental and physical capacity during the intervention. Additionally, to the supervised program, patients are instructed to do daily physical activity of at least 30 minutes by modalities accessible to the patient, e.g. in- or outdoor walking activities in bouts of minimum 10 minutes.

Every second session of the patient education consists of 25 minutes of Mindfulness-based Cognitive Therapy (MCBT) exercises and education developed for COPD patients with the potential mediating effects of mindfulness, self-compassion and breathlessness catastrophizing. The other education sessions consist of dialogue reflections around empowerment of the subjects: action-plan for symptom deterioration, medication-technic and correct use, better living with COPD, nutrition and importance of smoking cessation.

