The home visit is followed by once weekly structured web/phone call from the physiotherapist/nurse for 10-weeks using a motivational interviewing approach. During the telephone calls, the patient discusses the exercise, mindfulness program and exercise goals, and have the option to discuss other health issues in relation to COPD. A typical telephone call will begin with a brief talk of what has happened during the exercise program over the past week. Consistent with the principles of motivational interviewing, the physiotherapist/nurse might then ask the patient why she/he might want to increase the exercise program (desire); how she/he might do this if she/he decides to (ability); what would be the most important benefits in doing more exercise (reasons); and how important it is for the patient to do more exercise at this time (need). The physiotherapist will then encourage the participant to move towards commitment and action, with specific goal set for the following week. During each web/phone call the participants document their goals in their diaries in the same manner as from the initial home visit session. The discussion will then move on to other issues in relation to COPD. The patient is provided with a menu of topics relevant to COPD and self-care and encouraged to select a topic of relevance for discussion, providing opportunity for self-management. Education materials are delivered in hard copies together with the tablet and exercise equipment but also available as audio-book chapter on tablet in layman language. The book is called Better Living with Chronic Obstructive Pulmonary Disease – a patient guide. Exercise equipment is a package of a step-box and pairs of dumbbells weight from 1 to 5 kilo (heavier dumbbells available on request).

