### **3.7.3 Control**

Patients randomized to the control group will receive usual care; medication, scheduled follow-up visit and possible phone contact with GP or the outpatient respiratory department. Except for assessment visits 10-, 35-, and 75-weeks from baseline no intervention is offered.

If a patient changes his/her mind and wishes to participate in a conventional hospital- or community-based PR program, it will be granted as this is a highly recommended treatment (e.g. rehabilitation after hospital admitted exacerbation).

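### The primary visit is set at 10 weeks from baseline and labelled end of intervention, but with the stated start lag the 10-week programmes end at week 11.0 to 11.4

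*Protocol*

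**What the plan says.** **Order of events.** Section 3.2: "During inclusion, baseline self-reported symptoms, functional capacity and physical activity is measured. Hereafter each participant is randomly assigned". Section 3.6.2 agrees: "After written informed consent and completion of study assessments, patients are randomized to either HPR, PTR or CON". Neither section gives the interval between the two.

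**Start and length of the programmes.** Section 3.2: "The HPR and PTR interventions begin within seven-to-ten days after randomization and patients participate in the 10-week assigned intervention". Section 3.6.2 repeats the lag for every arm: "The patients in the three groups begin their assigned intervention within seven to ten days after randomization". The tele-rehabilitation programme (PTR) runs "two times per week for the duration of 10 weeks" (section 3.7.1). For the home-based programme (HPR), section 3.7.2 says: "The home visit is followed by once weekly structured web/phone call from the physiotherapist/nurse for 10-weeks".

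**Timing of the visits.** Section 3.2 puts the primary outcome at the 10-week visit and adds: "Follow-up assessment are done 10, 35 and 75 weeks (primary endpoint for the maintenance study) from baseline". The statistical section (3.6.1) also counts weeks 10, 35 and 75 from baseline. For the control arm (CON), section 3.7.3 says: "Except for assessment visits 10-, 35-, and 75-weeks from baseline no intervention is offered". The control row of Appendix 1 gives controls the same baseline-based schedule as the other two arms.

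**Label.** Table 1 heads the Week 10 column (Visit 1) as the end of the intervention.

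**The concern.** The protocol uses two reference points for Visit 1, a fixed time from baseline and the end of the programme. They coincide only if the programme starts on the day of baseline, whereas the protocol describes a later start. It gives no visit window and no rule for which reference point prevails.

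If the baseline clock is followed, the primary outcome is taken while the programme is still running but is presented as an end-of-intervention result. The estimate then describes an incomplete programme, and any benefit that comes late is missed in the comparisons with CON. If a site works from the Table 1 label instead, it must depart from the stated clock. Several hospitals are involved, so the conflict could be resolved differently from place to place.

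**Working it through.** **Inputs**
- Gap from baseline to randomisation, g: not stated. Taken as 0 days, which favours the protocol.
- Lag from randomisation to start, L: 7 to 10 days (sections 3.2 and 3.6.2). L = 0 is added in case the wording sets only an upper limit.
- Programme length: 10 weeks = 70 days (sections 3.2, 3.7.1, 3.7.2).
- Visit 1: day 70 from baseline (sections 3.2, 3.6.1, 3.7.3, Appendix 1).
- PTR sessions: 2 per week × 10 weeks = 20 (section 3.7.1).
- Maintenance: 65 weeks = 455 days (section 3.2).

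**Formulas**
- Programme end (day) = g + L + 70
- Programme days completed at Visit 1 = 70 − g − L
- PTR sessions held by Visit 1 = 2 × (days completed ÷ 7)
- Maintenance end (week) = (g + L + 70 + 455) ÷ 7

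**Results with g = 0**

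| Lag L | Programme end | Days completed at day 70 | PTR sessions held | Maintenance end |
|---|---|---|---|---|
| 0 days | day 70 = week 10.0 | 70 of 70 (100%) | 20.0 of 20 | 525 ÷ 7 = week 75.0 |
| 7 days | day 77 = week 11.0 | 63 of 70 (90%) | 18.0 of 20 | 532 ÷ 7 = week 76.0 |
| 10 days | day 80 = week 11.4 | 60 of 70 (86%) | 17.1 of 20 | 535 ÷ 7 = week 76.4 |

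The protocol's own figures, week 10 as the end of the intervention and 10 + 65 = 75 weeks, are reproduced only in the first row. That row needs baseline, randomisation and start on the same day.

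**Effect of g.** Each day between baseline and randomisation adds a day to the shortfall. Baseline includes accelerometer-measured activity, and randomisation follows completion of the assessments. If wear time runs on after the baseline visit, g exceeds 0. The protocol does not say how long that is.

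**PTR progression.** Appendix 1 gives PTR a last progression stage in weeks 7 to 10, which begins after 42 programme days. By day 70 a patient has had 63 − 42 = 21 or 60 − 42 = 18 of its 28 days, so 7 to 10 days are still to come. Appendix 1 gives HPR no such stage; that programme is adjusted individually each week.

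**The case against.** The strongest defence is that a fixed time from baseline in every arm is a valid intention-to-treat comparison. Four places in the protocol use that clock, and only one column heading points elsewhere. On this view the defect is a label. The validity of the comparison stands: followed as written, all arms are measured at the same time. But the label is attached to the primary visit and describes what the trial is taken to estimate, and the sum 10 + 65 = 75 weeks makes the same zero-lag assumption.

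Two further points stand as limits on size. The lag may be meant as an upper limit, in which case some patients start earlier and lose less. And 17 to 18 sessions exceed the 70% per-protocol threshold of section 3.6.1 (0.70 × 20 = 14), so that analysis set remains reachable by day 70.

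A visit window may be set in a document not shown. That would not settle which event the visit is counted from, which the protocol itself states in two incompatible ways.

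A reader might infer three stronger claims, none of which the protocol supports:
- *That the arms are measured at different times.* Appendix 1 gives controls the same schedule. A difference would arise only if sites tied the visit to programme end in HPR and PTR but kept CON at week 10.
- *That HPR and PTR have different lags because PTR patients wait for a group of 4 to 6 to fill.* One lag is stated for both, and nothing says that patients wait for a group.
- *That power falls by a calculable amount.* This needs an assumption about how benefit builds up over the ten weeks, and the protocol gives none. The 2.5 points in section 3.6 are a minimal clinical difference, not an expected effect at programme completion, so scaling them by exposure has no basis.

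**Conclusion.** The contradiction is real. With the stated lag of 7 to 10 days, week 10 from baseline is not the end of a 10-week programme. The programme ends at week 11.0 to 11.4, and the primary outcome is taken after at most 86% to 90% of it. This assumes that baseline and randomisation fall on the same day. The shortfall runs from 0 to 10 days if the lag is only an upper limit, and is larger if randomisation comes after the day of baseline.

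The likely direction is some dilution of HPR and PTR against CON. It is probably modest: near nil if benefit levels off early, more if it is still building at week 9. For HPR against PTR, no direction follows from the document. The point deserves correction because it concerns when the primary outcome is measured and can be settled by wording.

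**What to change.** Reconcile sections 3.2, 3.6.1, 3.6.2 and 3.7.3, Table 1 and the control row of Appendix 1 around one clock:

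1. Anchor Visit 1 in all three arms to one common time after the last scheduled session. One option is a fixed time from randomisation equal to the maximum start lag plus 10 weeks: 10 + 70 = day 80.
2. State one visit window for all arms.
3. Place the control arm's maintenance offer, which Appendix 1 makes after 10 weeks, explicitly after Visit 1. Otherwise moving the visit would let controls begin maintenance before the primary assessment.
4. Count the later visits from the same anchor. Keeping the present spacing puts them 35 − 10 = 25 and 75 − 10 = 65 weeks after Visit 1.
5. Correct the statement in section 3.6.2 that all three groups begin an intervention, since CON has none to begin.

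**Cost.** Visit 1 moves later by about 1 to 1.5 weeks (10 days = 1.4 weeks in the example). A patient who starts early has a short interval between last session and visit: 80 − 77 = 3 days with a 7-day lag, and at most 10 days with an immediate start. No visits or patients are added. With recruitment to March 2024, the last visit at week 76.4 from randomisation (about 17.6 months) falls around September 2025, inside the January 2026 limit in section 8.
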